## I. FUNDING AND SUPPORT IN KIND

| FUNDER(S)

(Names and contact details of ALL organisations providing funding and/or support in kind for this study) | FINANCIAL AND NON FINANCIALSUPPORT GIVEN     |
|---------------------------------------------------------------------------------------------------------------------------|----------------------------------------------|
| No project specific funding was received.                                                                                 | N/A                                          |
| King's College London                                                                                                     | Facilities for conducting the research study |

## II. ROLE OF TRIAL SPONSOR AND FUNDER

King's College London is the sponsor of the study, being responsible for conducting the research procedures as described in the protocol, analyses, interpretation, and dissemination of findings. appropriate standards, conduct and reporting are adhered to regarding its facilities and staff involved with the project.

### 1 BACKGROUND

ADHD is a neurodevelopmental disorder characterized by poor attention, heightened impulsivity, and hyperactivity (American Psychiatric Association, 2000). Within this, impulsivity can be divided into motor, temporal and cognitive impulsivity (Evenden, 1999; Jentsch et al., 2014; Yang, Vollm, & Khalifa, 2018). Although often considered a childhood disorder, its prevalence in adults is estimated at 2.5-5.2% and, critically, many people who meet the criteria for ADHD in adulthood did not meet the criteria as children (Moffitt et al., 2015). This means that research findings from children with ADHD may not apply to adults with the condition. Irrespective of age, psychostimulants (e.g., amphetamine) are the most common and efficacious treatment. They mainly act on dopamine (DA) and noradrenaline (NA) systems and are effective in over 80% of patients (Dittmann et al., 2014). However, whilst psychostimulants reduce ADHD symptoms, they have side effects ranging from insomnia to tachycardia (Mariani, Mariani, & Levin, 2007) and there are concerns about the drugs being abused (Darredeau, Barrett, Jardin, & Pihl, 2007). It is therefore important that other treatments are explored.

Preclinical studies suggest that other neurotransmitter systems might be involved in ADHD aetiology (e.g. Bolanos et al., 2008) and reduced brain serotonin (5-HT) levels have been reported in a well-validated animal model of ADHD (Sagvolden et al., 2005). Furthermore, altered genes relating to serotonin are implicated in ADHD in human research (Baehne et al., 2009; Grünblatt et al., 2012). Interestingly, dietary precursors can impact the synthesis rate and function of serotonin. Tryptophan (TRP) is such a dietary precursor and an essential amino acid involved in the synthesis of 5-HT which can modulate cognition and behaviour (Silber & Schmitt, 2010). Importantly, for this study, depletion of TRP has been associated with ADHD-like symptoms (Banerjee & Nandagopal, 2015) meaning that increasing tryptophan could offer a novel standalone or adjunct treatment in ADHD. To date, only a few studies have investigated TRP modulation in adults with ADHD. These studies have largely focused on secondary impairments rather than core symptoms, for example, examining reactive aggression (Kotting et al., 2013; Zimmermann et al., 2012), language processing (Grabemann et al., 2013) and memory processes (Zepf et al., 2013). Only one study to date examine attentional processes (Mette et al., 2013), meaning there is little or no research on the main cognitive symptoms of ADHD. Moreover, in all cases, the studies have used tryptophan depletion to infer a role for tryptophan in treatment, which assumes that those with ADHD have a high enough level

## Study Protocol: Tryptophan and Attention Deficit Hyperactivity Disorder

of serotonin production for the depletion to offer a significant reduction. This cannot be assumed given that the individuals may have very low levels to begin with. Based on this, the overall aim of the current study is to investigate the effects of moderating tryptophan levels on attention, motor, temporal and cognitive impulsivity in healthy and ADHD participants. To achieve this, we will assess the impact of acute tryptophan loading (low and high TRP supplementation), compared to a balanced (unmoderated tryptophan) control condition on key cognitive ADHD symptoms in:

1. Healthy control participants (HC) and unmedicated adults with a diagnosis of ADHD (ADHD-UM) to establish the effects of tryptophan on ADHD symptoms.
2. Medicated adults with ADHD (ADHD-M) in comparison to unmedicated adults with ADHD (ADHD-UM) to establish the effectiveness of tryptophan as an adjunct treatment for ADHD.

Details of supplementation: The balanced condition (BAL) contained only 40g of 100% whey powder which provided balanced amino acid availability and contained 0.566g of TRP. The low loading condition had added TRP resulting in 1.43g of TRP and the high loading condition contained 5.24g of TRP.

## 2 RATIONALE

Attention Deficit Hyperactivity Disorder (ADHD) affects around 3% of adults and is associated with reduced attention, high levels of impulsivity, hyperactivity and altered reward learning. At present adult ADHD is normally treated with psychostimulant medications (e.g. Ritalin or Adderall) but there are concerns about side effects, abuse potential and they do not work for everyone. It is therefore important to consider alternative approaches. Preliminary research suggests that modulation of tryptophan may be a suitable intervention but there is a lack of controlled research and very little research at all in adults.

## 3 OBJECTIVES AND OUTCOME MEASURES

### 3.1 Primary objectives

The purpose of the study is to assess the impact of acute tryptophan on attention and impulsivity in adults. We aim to see if tryptophan loading is effective in reducing the symptoms of ADHD in adults, both alone and in combination with ADHD medication.

### 3.2 Secondary objective

There are no secondary objectives.

### 3.3 Outcome measures

- Attention is measured using omission errors and hit reaction time on the Test of Variables of Attention (TOVA). Additionally, d' prime will be used as a measure of response sensitivity.
- Motor impulsivity is measured using commission errors on the TOVA.
- Temporal impulsivity is measured using the Delay Discounting Task (DDT) and specifically the area under the discounting curve.
- Cognitive impulsivity is measured using the Iowa Gambling Task (IGT) to assess risky decision making using a net score and percentage of risky decisions.

### 3.4 Primary outcomes

As detailed above.

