- Tests of impulsivity – two specific tests will be used to measure impulsivity. In the first test participants will be asked to make choices, using keyboard presses, between hypothetical rewards now or at a point in the future for several different delays e.g. 1 week, 2 weeks, 1 month, 3 months, 6 months and 1 year. In the second test participants will be shown 4 decks of cards (labelled A, B, C, and D) and asked to choose 100 times from the decks with two decks giving greater gains and losses. Additionally, the test of attention will also provide a further measure of impulsivity.

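### All seven task measures are primary with no lead measure or stated success rule, which leaves roughly a 16–27% chance of a false primary finding, and the IGT scores may count one result twice

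*Protocol*

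**What the plan says.** Protocol section 3.3 lists seven measures.

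- **TOVA, attention:** omission errors and hit reaction time, with d' added ("prime will be used as a measure of response sensitivity").
- **TOVA, motor impulsivity:** "Motor impulsivity is measured using commission errors on the TOVA".
- **DDT, temporal impulsivity:** area under the discounting curve.
- **IGT, cognitive impulsivity:** assessed "using a net score and percentage of risky decisions".

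Section 3.4 (Primary outcomes) reads, in full, "As detailed above". Section 3.5 (Secondary outcome) is marked not applicable, and section 3.2 says "There are no secondary objectives". The table in section 3.6 sets the three tasks together against one primary objective, unranked.

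Section 7 describes the IGT: participants are "asked to choose 100 times from the decks with two decks giving greater gains and losses", with four decks in all. Section 9.1 gives one sample size, 144 at power 0.95, without naming a measure or an ANOVA effect. Section 9.3.1 plans a 3 x 3 x 2 mixed ANOVA, with transformations where needed. No significance level is stated.

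**The concern.** Choosing the primary outcome is the protocol's job, and section 3.4 does it by making everything primary. A trial with seven primary measures, no ranking and no statement of how many must succeed does not say what a positive result is. Whichever measure reaches significance can be put forward as the primary finding, and the error rate of that claim is well above the level of each single test.

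The list also contains overlap. The two IGT scores may be one quantity on two scales, in which case a single chance result would look like two agreeing primary results. d' is normally built from hit and false-alarm rates, and omission and commission errors carry the same information. The sample size is not tied to any of the seven.

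**Working it through.** **1. The protocol's own figure.** Section 9.1 gives N = 144 at power 0.95 for a small-to-medium effect. Effect size f, alpha, within-subject correlation and tested effect are not given, so the figure can be neither confirmed nor refuted. Assume alpha 0.05, correlation 0.5, two time points, nine cells, and noncentrality N x f² x 2/(1 − 0.5). Then 144 gives 95% power at f of about 0.166 (2 df), 0.183 (4 df) or 0.205 (8 df). That is compatible with the wording, but for one test on one measure.

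**2. Count.** TOVA 4 + DDT 1 + IGT 2 = 7 primary measures, 0 secondary. If the two IGT scores coincide (step 4), at most 6 are distinct.

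**3. Chance of at least one false positive, one tryptophan effect per measure, alpha 0.05 assumed.**

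| Measures | Correlation between tests | Chance |
|---|---|---|
| 6 | 0 | 1 − 0.95^6 = 26.5% |
| 6 | 0.3 | 24% (simulated) |
| 6 | 0.5 | 21% (simulated) |
| 6 | 0.7 | 16% (simulated) |

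The simulated rows use six equally correlated two-sided normal tests, 400,000 draws each. If both condition x time and group x condition x time are read on each of six measures, there are 12 tests, and under independence 1 − 0.95^12 = 46%.

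**4. IGT identity (conditional).** Let R of the 100 choices be risky. Percentage risky = R. If net score is safe minus risky picks, net = (100 − R) − R = 100 − 2R. The correlation is exactly −1, and an untransformed ANOVA gives the same F and p for both.

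**5. Cost of a Holm correction over four domains.** With N = 144, f = 0.20 and correlation 0.5, the noncentrality is 144 x 0.04 x 2/0.5 = 23.04, with error df 144 − 9 = 135. The first Holm step is at 0.05/4 = 0.0125.

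| Effect | Critical F at 0.05 | Power | Critical F at 0.0125 | Power |
|---|---|---|---|---|
| 8 df (all nine cells x time) | 2.01 | 94% | 2.56 | 84% |
| 4 df (group x condition x time) | 2.44 | 98% | 3.32 | 93% |
| 2 df (condition x time) | 3.06 | 99% | 4.53 | 97% |

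**The case against.** **No rule says any single success is enough.** This is true. The protocol gives no success criterion, and the four domains could each be reported separately. A reader might infer that the trial plans to claim success on any one measure, but the text does not say so. What stands is that nothing rules it out.

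**Multiplicity adjustment may sit in an SAP that is not shown.** This is also fair, and its absence from the protocol is not the point. The point is the stated designation: an SAP that singled out one measure would contradict sections 3.4 and 3.5.

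**The error rate is easily overstated.** A reader might quote 1 − 0.95^7 = 30% for seven tests, or 1 − 0.95^28 = 76% for two loading contrasts in each of two ADHD groups on seven measures. Neither is supported. Both treat the measures as independent, which cannot hold if two IGT scores coincide and d' overlaps the error counts. The 28-test family is not in the protocol, which plans a mixed ANOVA. Even if that family is taken, simulation with six distinct measures and a shared balanced arm gives about 68% at correlation 0 and 48% at 0.7.

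**The IGT duplication is assumed.** Section 3.3 gives no formula, and section 7 speaks of gains and losses, so a monetary net score is not excluded. Different transformations or trial blocks would also break the identity. It would therefore be wrong to state as fact that the two scores are the same number. Likewise, d' overlaps with the error measures without duplicating them; it answers a different question from either error count.

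**Conclusion.** The point holds. The protocol makes seven measures primary, ranks none and leaves none secondary. The inflation is material but moderate: about 16% to 27% for one effect per measure over six distinct measures, against a nominal 5%. This assumes alpha 0.05 and correlations between 0.7 and 0. It is higher if several effects or contrasts per measure are read, but the protocol does not fix such a family, so no single larger figure can be assigned.

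The double counting on the IGT is conditional on net score meaning safe minus risky picks, with both scores analysed untransformed over the same 100 choices. If another meaning is intended, the protocol needs to say so.

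**What to change.** Before unblinding:

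1. In section 3.4, name either a single primary measure or one per domain (attention, motor, temporal and cognitive impulsivity). The sponsor chooses which.
2. Name the one ANOVA effect tested on each, for example condition x time or group x condition x time. Without this, Holm has no defined set of tests to work on.
3. If more than one primary test remains, apply Holm across them at a stated alpha.
4. Move the remaining measures to section 3.5 as secondary.
5. Define IGT net score in section 3.3, and keep only one IGT score if the two are the same quantity.

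This needs wording changes only, with no new data or procedures. The downside is the stricter threshold in step 5 of the working: with four domains the first Holm step takes an 8-df effect at f = 0.20 to 84% and a 4-df effect to 93%, both below the planned 0.95, while a 2-df effect stays at 97%. A single primary measure with one named effect avoids that loss.

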### 3.5 Secondary outcome

N/A.

### 3.6 Table of outcomes

| Objectives                                                                                                                                                                                                                                                        | Outcome Measures | Timepoint(s) of evaluation of this outcome measure (if applicable)                                                                                |
|-------------------------------------------------------------------------------------------------------------------------------------------------------------------------------------------------------------------------------------------------------------------|------------------|---------------------------------------------------------------------------------------------------------------------------------------------------|
| Primary Objective: To assess the impact of tryptophan loading on attention and impulsivity in adults with ADHD, both alone and in combination with ADHD medication (psychostimulants or non-stimulants) with a healthy control (non-ADHD) reference group. | TOVA, DDT, IGT   | Tests will be conducted before tryptophan loading at the start of the laboratory session and again 1 hour after consumption of the protein drink. |

## 4 TRIAL DESIGN

Double blind randomised controlled trial with randomisation stratified by group (ADHD-M, ADHD-UM, HC) and gender (male female) into three different tryptophan conditions, creating a 3 (participant group) x 3 (tryptophan modulation) x 2 (time, before and after) design.

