## 9 STATISTICS AND DATA ANALYSIS

### 9.1 Sample size calculation

There is no existing data to calculate considering these groups and conditions to sample size. However, similar studies covering components of the current work, indicate small-medium effects sizes, therefore a power analysis assuming this effect size and power of 0.95 was conducted. This suggests that we require a total group size of 144 participants (48 HC, 48 ADHD-M, 48 ADHD-UM).

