### 9.3 Statistical analysis plan

#### 9.3.1 Primary and secondary outcome analysis

To achieve the study's objectives, we will adopt a 3 x 3 x 2 factorial design. Factor 1, 'ADHD Status', is a between-subjects factor and consists of three distinct participant groups (healthy controls, unmedicated ADHD, medicated ADHD). Factor 2, also between-subjects, is 'Tryptophan modulation' and consists of three conditions: balanced, low loading, high loading. The final factor is within-subjects and is the 'Time' at which measures are collected i.e., before and after protein (tryptophan) consumption. Data analysis will use parametric methods, typically mixed ANOVA, after normality checks and any necessary transformations.

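### Randomisation is stratified by gender, but the stated 3 x 3 x 2 mixed ANOVA leaves gender out; gender and gender x time should be added as adjustment terms

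*Protocol*

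**What the plan says.** Section 4 (Trial design) describes a double-blind trial with "randomisation stratified by group (ADHD-M, ADHD-UM, HC) and gender (male female) into three different tryptophan conditions". The same sentence goes on to "creating a 3 (participant group) x 3 (tryptophan modulation) x 2 (time, before and after) design", in which gender no longer appears.

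Section 9.3.1 repeats the structure: "we will adopt a 3 x 3 x 2 factorial design". It then goes through the factors one at a time: ADHD status (between subjects), tryptophan modulation (between subjects) and, to close the list, "The final factor is within-subjects and is the 'Time' at which measures are collected". On method it says: "Data analysis will use parametric methods, typically mixed ANOVA, after normality checks and any necessary transformations".

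No covariate is named, and gender has no role in any analysis statement. Section 7 shows that gender is recorded in the screening survey. Section 9.1 fixes 48 participants in each of the three groups but sets no gender quota, and no section mentions matching the groups on gender.

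**The concern.** A factor judged important enough to stratify on would normally also enter the analysis. If it predicts the analysed quantity and is left out, its variance stays in the error term although the allocation has already removed it from the treatment comparison. The standard error is then too large.

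A second issue concerns participant group, which is observed and not randomised. Stratifying within group balances gender across the three drinks inside each group. It does nothing to balance gender between HC, ADHD-UM and ADHD-M. Any statement about how the groups differ, in level or in pre-post change, is open to a gender difference between them, and the stated model cannot remove it.

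**Working it through.** **Inputs from the protocol.** N = 144, 48 per group (9.1); three groups, three conditions, two times (4 and 9.3.1); stratification by group and gender (4). The protocol gives no gender mix, gender effect or pre-post correlation.

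**The plan's own figure.** 144 is stated at power 0.95 for an effect size described only as small to medium. With no numerical effect size, alpha, correlation or tested term, it can be neither confirmed nor refuted, and the present point does not depend on it.

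**Assumptions for the check.** Equal allocation (16 per group-by-condition cell), outcome SD 1, pre-post correlation 0.5, alpha 0.05. The variance of the change within gender is then 2 x (1 - 0.5) x 1 = 1. Rejection rates come from 20,000 simulated trials per scenario, so the Monte Carlo standard error near 0.05 is sqrt(0.05 x 0.95 / 20,000) = 0.0015.

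**Step 1: which terms carry the treatment question.** In a pre/post mixed ANOVA these are tryptophan x time and group x tryptophan x time, both tested on the change post minus pre. A gender effect on level is present at both times and cancels.

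**Step 2: gender predicts the change.** With a 50/50 mix and a gender difference g in change, omitting gender multiplies the error variance by v = 1 + g²/4. For a 2-df test in large samples the true size is 0.05^v, because the chi-square tail on 2 df is exp(-c/2).
- g = 0.2: v = 1.01, size 0.05^1.01 = 0.0485
- g = 0.5: v = 1.0625, size 0.05^1.0625 = 0.0415
- g = 1.0: v = 1.25, size 0.05^1.25 = 0.0236

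Simulation, gender omitted vs gender and gender x time included, 24 of 48 of one gender in each group:

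| Gender effect | Tryptophan x time, type I | Three-way, type I | Power for tryptophan x time at a 0.6 SD effect |
|---|---|---|---|
| Level only, 0.5 SD | 0.049 vs 0.049 | 0.052 vs 0.052 | 0.865 vs 0.865 |
| Level only, 1.0 SD | 0.050 vs 0.050 | 0.051 vs 0.051 | 0.860 vs 0.861 |
| Change, 0.2 SD | 0.048 vs 0.050 | 0.048 vs 0.050 | 0.859 vs 0.862 |
| Change, 0.5 SD | 0.040 vs 0.048 | 0.038 vs 0.050 | 0.836 vs 0.856 |
| Change, 1.0 SD | 0.021 vs 0.048 | 0.018 vs 0.051 | 0.773 vs 0.858 |

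The hand formula and the simulation agree closely.

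**Step 3: group terms.** If the proportions of one gender in two groups differ by p1 - p2, the bias in their difference is (p1 - p2) x gender effect. Take an assumed mix of 36, 24 and 18 of 48 (0.75, 0.50, 0.375):
- A 0.5 SD gender effect on level biases the most distant pair by 0.375 x 0.5 = 0.19 SD. The group main effect then rejects a true null in 0.126 of trials with gender omitted and 0.051 with it included.
- Adding a 0.3 SD gender difference in change biases the same pair's change by 0.375 x 0.3 = 0.11 SD. Group x time rejects in 0.069 vs 0.050.
- With the level effect alone, tryptophan x time is unaffected by the unequal mix: 0.048 vs 0.048.

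With an equal mix the direction reverses. The group main effect is conservative at 0.037 vs 0.049 for a 0.5 SD level effect.

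**Step 4: which terms to add.** A gender main effect enters only the between-subject stratum. The within-subject error is built from change scores, so only gender x time reduces it. Error df go from 144 - 9 = 135 to 134 in each stratum.

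**The case against.** The strongest reply is that a covariate list is usual SAP content, that 9.3.1 says only that mixed ANOVA is typical, and that 3 x 3 x 2 describes the design and excludes nothing. Part of this stands: a separate SAP may add gender. But 9.3.1 sits under a heading for the statistical analysis plan, lists its factors and closes the list. Anyone following it as written would leave out a factor that section 4 stratifies on.

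A reader might infer that the omission makes the treatment tests conservative in general. The documents do not support that. The stated analysis is pre/post, a stable gender effect drops out, and nothing in the protocol suggests that gender shifts the change within one session. Where it does, the error is on the safe side.

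A reader might also infer that the treatment comparison is biased, or that the group comparisons are in fact confounded. The first fails because conditions are randomised within each group by gender. The second cannot be known, because no gender mix is given. The objective in section 3 also concerns tryptophan loading, with healthy controls as a reference group, so the exposed terms are not the central ones.

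Finally, if gender modifies the tryptophan effect itself, adjustment does not cure the three-way term. At an assumed 1.0 SD interaction with the unequal mix, it rejects in 0.069 of trials with gender omitted and 0.075 with it adjusted for. That limit stands.

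**Conclusion.** The mismatch between design and stated model is certain; its consequences are modest and conditional. The randomised tests stay valid. They lose about 2 power points, with tryptophan x time type I error near 0.040, if gender shifts the pre-post change by 0.5 SD. At 0.2 SD almost nothing is lost, and if gender affects level only, nothing is. The group main effect and group x time can be confounded, but only if the gender mix differs between groups. The 0.126 and 0.069 above illustrate assumed mixes and effects and do not estimate what this trial will show. Conservatism and confounding are not simultaneous faults of one group test: which arises depends on the mix. The correction is worth making because it costs almost nothing, not because the primary conclusions are at risk.

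**What to change.** In 9.3.1, state that each primary mixed ANOVA includes gender, coded as for stratification, and gender x time as adjustment terms, or give the reason for leaving them out. They should not be crossed with group and tryptophan. Full crossing gives 3 x 3 x 2 = 18 between-subject cells averaging 144/18 = 8 participants and uses 18 - 9 = 9 degrees of freedom. The adjustment proposed here uses about one error df in each stratum (135 to 134), takes one sentence and needs no new data. It would also help to say that the group main effect and group x time are observational comparisons and to report the gender mix by group. A possible gender-by-tryptophan interaction is a separate question that this change does not answer.
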